#### Exclusion criteria

Bank workers who have at least one of the NCEP: ATP III metabolic syndrome criteria but with dietary restrictions and absolute contraindication for physical activity due to musculoskeletal, neurological, vascular, lung and cardiac problems, pregnant mothers, those who have a plan to be pregnant within the intervention months and diagnosis of severe psychiatric disorders, significant cognitive impairment, and those who will not available throughout the program will be excluded from the study.

### Sample size

Because researchers can use mean and standard deviation (SD) from previous studies in a similar context to estimate sample size [26]. We utilized the mean and SD from a study at Jimma University among university staff to evaluate the effectiveness of behavior change communication on metabolic syndrome among Ethiopian adults in a randomized controlled trial [27]. The sample size for this randomized control trial study was determined under the assumptions and using the formula of the sample size calculation for randomized control trial studies with continuous outcome variables [26]. Since blood pressure is the study’s primary outcome measure and the most common indicator of metabolic syndrome among bank employees in Bahir Dar city and also gives a maximum sample size among other indicators, the means and standard deviations of systolic blood pressure were taken from a study with a similar design that was conducted in Ethiopia [27], and a power of 80%, a 1:1 ratio, and a 95% confidence interval were used. Then the sample size was calculated as follows;

$$n1=\frac{(\sigma 1^{2}+\sigma 2^{2}){\;[Z1‐\alpha /2+Z\;1‐\beta ]}^{2}}{{\left(M1‐M2\right)}^{2}}$$

$$n1=\frac{(15.0^{2}+16.3^{2})\;{\left[1.96+0.84\right]}^{2}}{{\left(107.8‐114.2\right)}^{2}}=\frac{(225+265.69)\;{\left[2.8\right]}^{2}}{6.4^{2}}=\frac{\left(490.69)(7.84\right)}{40.96}=94$$

n1 = 94 and n2 = n1*1 = 94, Therefore, N = n1+n2 = 188

where,

m1 = mean of systolic blood pressure for the intervention group

m2 = mean of systolic blood pressure for the control group

σ1 = standard deviation of systolic blood pressure for the intervention group

σ2 = standard deviation of systolic blood pressure for the control group

n1 = sample size for group 1

n2 = sample size for group 2

α = probability of type I error (usually 0.05)

β = probability of type II error (usually 0.2)

z = critical Z value for a given α or β

N = Total sample size

By taking into account a 20% attrition rate, 226 total individuals or 113 individuals per group will be recruited for the study.

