**Methods and analysis:**

This randomized controlled trial will be implemented with 226 bank employees (age ≥18 years) with metabolic syndrome from government and private banks in Bahir Dar City, Ethiopia. Participants will be randomized to intervention (education) and control (general health advice) groups. The intervention group will be given one-on -one base education about healthy diets, physical exercise, stress management, avoidance of harmful alcohol consumption and smoking cessation by experts on health promotion. Text messages will be sent every two weeks and reading materials will also be provided. Additionally, a review meeting will be held at the 3^rd^ and 6^th^ month of the intervention. The primary outcomes of interest will be change in metabolic parameters (obesity levels, blood pressure, fasting blood glucose, total cholesterol, high density lipoprotein, low density lipoprotein, and triglycerides). Secondary outcomes will be knowledge, attitudes and practice of the participants towards lifestyle and cardiovascular risk factors, feasibility, acceptability, implementation fidelity, and cost-effectiveness of the intervention. Data will be collected at three time points: at baseline, at the 6^th^ month of the intervention and at the end of the intervention (9 months). Generalized linear mixed models will be utilized to compare the desired outcome between the trial arms, after accounting for baseline variations. Cost-benefit analysis and a qualitative process evaluation of the intervention will also be conducted.

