### Dependent variables

#### Primary outcomes

*Body size (Central obesity)*. These will be defined as waist circumference > 102 cm in men, > 88 cm in women [2], and will be measured with a tape measure at the approximate midpoint between the lower margin of the last palpable rib and the top of the iliac crest or at the abdomen’s maximum extension. It will be measured at the baseline and 9^th^ month of the intervention.

*Blood pressure (BP)*. Which is defined as BP ≥ 130/85 mmHg [2, 28], and will be measured as follows: Three blood pressure measurements will be taken using appropriate size sphygmomanometer after the person is taking a rest for 5 minutes for the first measurement and with a difference of 5 minutes between successive measurements. The mean systolic and diastolic BP measurements will be considered for interpretation. The measurement will be taken at the baseline and the 9^th^ month of the intervention.

*Biochemical markers*. Fasting blood glucose (FG), high density lipoprotein (HDL), and triglycerides (TGL)) which are defined as fasting glucose ≥110 mg/dl, HDL-cholesterol < 40 mg/dl in men and < 50 mg/dl in women and Triglycerides ≥150 mg/dl respectively [2]. From each eligible individual 5 ml of venous blood will be collected at baseline and at the end of the intervention before breakfast by employing infection prevention procedures. Plasma and serum will be separated by laboratory technologist and stored at -80°C for later analyses at Bahir Dar University teaching hospital laboratory department. The tests will analyze FG, total cholesterol, HDL-C and TGL, while low-density lipoprotein will be determined indirectly.

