### Statistical analysis

The analysis will follow modified intention-to-treat principles (based on group randomized to and using all available data but without being able to directly assess the impact of the intervention being offered to those for whom we do not have follow-up data and where their outcome data are not missing at random). Descriptive statistics means (standard deviations), medians (interquartile ranges), frequencies (relative frequencies) will be used to summarize participant’ characteristics and study outcomes. Epi Data (double entry) will be used to enter the quantitative data and it will be analyzed using Stata 13.1 or later versions, with p<0.05 considered significant. Generalized linear mixed models (GLMM) will be used to assess the impact of the intervention on the change of metabolic syndrome components, as well as on the knowledge, attitudes and practice of participants on healthy lifestyle. The metabolic syndrome indicators (Obesity level, BP, FG, HDL, and TGL), knowledge, attitudes, and practices towards lifestyle and cardiovascular risk factors will be the outcome variables, and age, sex, marital status, educational status, work experience, working hours per day, monthly income, religion, health condition, and level of KAP will be the independent variables of the study.

All items in the CONSORT statement will be followed when reporting, and a CONSORT flow diagram will be included to indicate participant flow and, if available, the causes of exclusion and loss to follow-up (**Fig 1)**. The effectiveness of the intervention will be assessed using differences in changes in the metabolic syndrome indicators (Obesity level, BP, FG, HDL, and TGL) between groups from baseline to nine months. As well as, by assessing knowledge, attitudes, and practices towards lifestyle and cardiovascular risk factors before and after the intervention as well as between the control and intervention groups.

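### The protocol names one, seven or five primary outcomes depending on the section, while the sample size and the 5% error rate fit only one of them

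*Protocol article*

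**What the plan says.** Four places in the protocol article describe what is primary.

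- **Sample size.** Blood pressure, in the singular, is the study's "primary outcome measure and the most common indicator of metabolic syndrome among bank employees in Bahir Dar city". The calculation uses means and SDs of systolic pressure only, with 80% power and a two-sided 5% level.
- **Abstract, Methods and analysis.** The primary outcomes, in the plural, are changes in seven parameters: "obesity levels, blood pressure, fasting blood glucose, total cholesterol, high density lipoprotein, low density lipoprotein, and triglycerides".
- **Dependent variables, Primary outcomes.** Five measures receive a definition: waist circumference, blood pressure, and the markers given as "Fasting blood glucose (FG), high density lipoprotein (HDL), and triglycerides (TGL". Total cholesterol and LDL appear under this heading only as laboratory work: "The tests will analyze FG, total cholesterol, HDL-C and TGL, while low-density lipoprotein will be determined indirectly". The definitions are cut-offs. For blood pressure: "Which is defined as BP ≥ 130/85 mmHg".
- **Statistical analysis.** Effectiveness is judged "using differences in changes in the metabolic syndrome indicators (Obesity level, BP, FG, HDL, and TGL) between groups from baseline to nine months". That is five indicators, without total cholesterol and LDL. One threshold covers everything: "with p<0.05 considered significant".

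**The concern.** A reader cannot tell from this document which result decides whether the intervention worked. The trial is powered for systolic pressure alone, but the analysis section treats five indicators alike. An improvement in triglycerides or waist could then be reported as a primary success while the only powered outcome shows nothing. The introduction says the evidence is meant to support policy makers in scaling the programme up, so it matters which result carries the claim.

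Two outcomes declared primary in the abstract also have no place in the listed analysis. They would either go unreported as primary or be added later by choice.

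**Working it through.** **1. The plan's own sample size.** Inputs from the Sample size section: SDs 15.0 and 16.3, means 107.8 and 114.2, z values 1.96 and 0.84.

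n per group = (15.0² + 16.3²) × (1.96 + 0.84)² / (107.8 − 114.2)² = 490.69 × 7.84 / 40.96 = 93.9, so 94.

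The stated figure reproduces. It is a calculation for one outcome tested once at two-sided 0.05.

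**2. Count of primary outcomes by section.**

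| Section | Primary outcomes | Total cholesterol and LDL |
|---|---|---|
| Sample size | 1 (blood pressure; systolic used) | no |
| Abstract | 7 | yes |
| Primary outcomes | 5 defined | assays only |
| Statistical analysis | 5 analysed | no |

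The operative count is five, because only five are listed for testing. It becomes six if systolic and diastolic pressure are tested separately.

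**3. Error rate if any one of them may be claimed.** With k independent tests at 0.05 and no true effect, the chance of at least one false positive is 1 − 0.95^k.

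- k = 5: 1 − 0.7738 = 22.6%
- k = 6: 1 − 0.7351 = 26.5%

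The indicators are unlikely to be independent, and the document gives no correlations. As an assumption, let all test statistics share one correlation ρ. Each is then √ρ × (shared standard normal) + √(1 − ρ) × (own standard normal), and a false positive is any absolute value above 1.96. Simulation with 400,000 draws per setting gives:

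| ρ (assumed) | 5 tests | 6 tests |
|---|---|---|
| 0.3 | 20.9% | 24.1% |
| 0.5 | 18.3% | 20.7% |
| 0.7 | 14.8% | 16.4% |

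Every entry is about three to five times 5%.

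**4. Price of keeping several primaries.** With a Bonferroni split and the planned 6.4 mmHg systolic difference (root-mean-square SD 15.66), the results are:

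- Five outcomes, 0.05/5 = 0.01 each: power at 94 per group falls from 80% to 59%, and 140 per group would be needed.
- Six outcomes, 0.05/6 = 0.0083 each: power falls to 56%, and 146 per group would be needed.
- One outcome, systolic pressure, at 0.05: 94 per group stands.

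**The case against.** The strongest reply is that a multiplicity method or a rule for success is often left to the statistical analysis plan, which is not shown. That stands: a missing adjustment is not the finding. The finding is that this document names three different primary sets. An analysis plan could not follow all four sections at once.

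The Sample size section also says blood pressure gives the largest sample size among the indicators, which may suggest that the others are covered. That concerns power for each test taken alone at 0.05. It does not control the error rate when any one success counts. Nor does it carry the 80% over to joint success if all must succeed.

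Two stronger readings are tempting, and the document supports neither.

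- A reader might combine the abstract's seven outcomes with the 0.05 threshold and quote 1 − 0.95⁷ = 30%, or more with diastolic pressure counted separately. But outcomes missing from the listed analysis cannot add false positives to it. The two methods sections agree on five.
- A reader might take the cut-offs in the Primary outcomes section as the analysed form and conclude that power falls well below 80%. No section says blood pressure will be compared as a proportion. The abstract speaks of change, the sample size formula is for continuous outcomes, the mean of the readings is what is interpreted, and the analysis compares changes from baseline. The cut-offs repeat the metabolic syndrome criteria used for eligibility. The wording needs tidying, but it does not support a power figure.

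**Conclusion.** The contradiction over the primary outcome is real and can be seen within this one document. Its consequence is conditional. If any of the five or six listed tests can be claimed as a primary success, the chance of at least one false positive is 23 to 26% under independence and about 15 to 24% at assumed common correlations of 0.3 to 0.7, against the 5% used for sizing. If blood pressure alone decides, as the Sample size section implies, the other sections are simply wrong about what is primary.

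These figures take each individual test to have a true 5% level. The Randomization section allocates two parts of the city by coin toss, which raises a separate question about that level. Neither the figures nor the fix address it.

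**What to change.** Name one primary outcome that matches the sample size calculation: systolic blood pressure at nine months, continuous, as the mean of the three readings, compared between arms with adjustment for baseline systolic pressure at two-sided 5%. The choice of systolic has to be written down, because the Sample size section names only blood pressure and uses systolic values for the calculation.

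Make diastolic pressure, waist circumference, fasting glucose, HDL, triglycerides, total cholesterol and LDL secondary. List them identically in the abstract, the outcomes section and the Statistical analysis section. State that the cut-offs in the outcomes section are not the analysed form of the primary outcome. A formal correction across the secondary outcomes is optional and is not needed to resolve the contradiction.

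The sample size of 94 per group does not change. The cost is that the other metabolic indicators lose primary status. Recruitment began in November 2023, and the protocol commits to reporting important modifications to the ethical review board and the registry. The change must therefore be notified to both, and it should be fixed before anyone sees outcome data by arm.

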### Randomization

Bahir Dar city is divided in to two parts by the Nile River. From these two parts of the city, one will be randomly selected as the control area using a coin tossing randomization procedure by a principal investigator, and the other will assign as the intervention site. To reduce information contamination, bank employees who work in the control area will make up the control group, whereas bank employees who work in the intervention area will make up the intervention group. The data collectors, the nurse who will offer general advice to the control group, the education provider for intervention group, and the participants will all be blinded to the group assignment. Finally, each individual participant will be screened based on the inclusion and exclusion criteria, up until the target sample size is reached.

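### The stated 80% power assumes independently randomised individuals, but one coin toss allocates two areas, so the design as described does not have that power

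*Protocol article*

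**What the plan says.** The Sample size section of the protocol article states that the number was found "using the formula of the sample size calculation for randomized control trial studies with continuous outcome variables". For the inputs it says "a power of 80%, a 1:1 ratio, and a 95% confidence interval were used", and the formula uses a two-sided 5% level. The expected difference in systolic blood pressure is 6.4 mmHg (107.8 against 114.2), with standard deviations of 15.0 and 16.3. The result is "n1 = 94 and n2 = n1*1 = 94, Therefore, N = n1+n2 = 188", raised to 226 for attrition. No ICC, cluster size or design effect appears.

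The Randomization section describes a different design. The city has two parts, of which "one will be randomly selected as the control area using a coin tossing randomization procedure by a principal investigator", and the other becomes the intervention site. Membership follows workplace: "bank employees who work in the control area will make up the control group", and the same applies to the intervention area. The Study setting section gives 210 branches and 2,310 workers.

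The Statistical analysis section says "Generalized linear mixed models (GLMM) will be used to assess the impact of the intervention". Its list of independent variables contains individual characteristics only. It names no area or branch term and does not state the random effects.

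**The concern.** The formula treats the two arm means as averages of independent people. Here the randomised unit is an area, with one per arm, and employees are nested in branches that all take the arm of their area. Anything that makes people in one area or branch resemble each other adds variance to the difference between arms that the formula leaves out.

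Two things are at stake. The sample size justification claims a power that the allocation does not deliver. And if the between-arm comparisons are analysed as though individuals had been randomised, their confidence intervals will be too narrow and their p-values too small, to a degree that the trial itself cannot measure at area level.

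**Working it through.** **Inputs from the protocol article.** Difference 6.4; sum of variances 15.0² + 16.3² = 490.69; z values 1.96 and 0.84; 94 per arm; one area per arm; 210 branches and 2,310 workers, so 2,310/210 = 11 workers per branch on average.

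**Assumed, because the document gives no value.** ICC at area and branch level, and participants per branch. If recruitment were spread over all branches the latter would be 226/210 = 1.08; the ceiling is about 11, the whole staff of an average branch.

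**Step 1: the plan's own figure.** n = 490.69 × (1.96 + 0.84)² / 6.4² = 490.69 × 7.84 / 40.96 = 93.92, so 94. With 94 per arm, power = Φ(6.4/√(490.69/94) − 1.96) = 80.0%. The arithmetic is correct for independent individuals.

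**Step 2: area level.** With m = 94 in the single area of each arm:

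- Design effect DE = 1 + 93 × ICC.
- Power = Φ(6.4/√(490.69/94 × DE) − 1.96).
- Type I error of a test that ignores area = 2Φ(−1.96 × √((1 − ICC)/DE)), since such a test sees only the within-area variance.

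| Assumed area ICC | DE | Power | Type I error if area is ignored |
|---|---|---|---|
| 0.001 | 1.09 | 76% | 6% |
| 0.005 | 1.47 | 64% | 11% |
| 0.01 | 1.93 | 52% | 16% |
| 0.02 | 2.86 | 38% | 25% |
| 0.05 | 5.65 | 22% | 42% |

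The power column is a best case because it treats the between-area variance as known. With one area per arm there are zero degrees of freedom to estimate it. As the number per area grows, the variance of the difference cannot fall below 490.69 × ICC. So above an ICC of about 1/94 = 0.0106, no number of employees reaches 80%.

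**Step 3: branch level alone, taking the area effect as zero.** DE = 1 + (m − 1) × ICC, with the same power formula, 94 per arm and an assumed ICC of 0.05:

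| Participants per branch | DE | Power |
|---|---|---|
| 1.08 | 1.004 | 80% |
| 4 | 1.15 | 74% |
| 6 | 1.25 | 71% |
| 10 | 1.45 | 64% |

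**Step 4: possible offset from baseline adjustment.** With baseline as a covariate and an assumed baseline correlation of 0.5, the variance is multiplied by 1 − 0.5² = 0.75. At branch ICC 0.05, power becomes about 85%, 82% and 77% for 4, 6 and 10 per branch. An analysis of simple change scores at the same correlation has variance factor 2 × (1 − 0.5) = 1 and gains nothing.

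**The case against.** The best case for the plan has three parts.

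**Branch clustering may cost little.** Letters go to each branch, and at about one participant per branch almost no power is lost. The abstract says that baseline variation will be accounted for, and Step 4 shows that this could offset modest branch clustering. Both points stand, so the branch figures alone do not prove that power is below 80%. However, nothing in the article limits enrolment per branch, and the sample size calculation takes no credit for baseline adjustment. Adjustment may also remove a stable, measured difference in level between areas, but it cannot remove an area-specific shift over the nine months.

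**The model may already handle clustering.** A reader might infer from the list of covariates that the analysis omits clustering. The article does not show that. It names a mixed model, leaves its random effects unstated, and may leave them to a full analysis plan. All that can be said is that the model as described names no area or branch term.

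**Mechanisms of correlation are not documented.** A reader might suppose that co-workers attend the same education sessions. The Intervention section says that education is one-on-one, and although review meetings are held at months 3 and 6, it does not say that they are organised by branch. The point does not need such mechanisms: the mismatch between formula and unit of allocation is there without them.

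None of these arguments reaches the area level. Whatever the model, one area per arm leaves area and treatment inseparable.

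**Conclusion.** The point stands as a mismatch between the sample size formula and the allocation. The 80% is correct arithmetic for a design in which individuals are randomised, and the Randomization section describes another. It would apply here only with no area effect and negligible branch correlation, and the article states neither assumption.

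The size cannot be fixed at one number. Over assumed area ICCs of 0.001 to 0.05, best-case power runs from about 76% to 22%, and the type I error of a test that ignores area from about 6% to 42%. Branch clustering by itself ranges from no material loss to about 64% power at ten per branch and ICC 0.05, before any gain from baseline adjustment.

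Two stronger readings should be resisted. One is that true power is a particular figure such as 52%: that rests on an ICC the document does not give. The other is that a branch random effect, or few participants per branch, would restore the stated power: neither touches the area level, where between-area variance cannot be estimated.

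**What to change.** 1. In the Sample size section, remove the unqualified 80%. Restate power over a stated range of branch ICC and participants per branch using 1 + (m − 1) × ICC, and say explicitly that the figures assume no area effect.
2. Record branch for every participant, and include a branch random intercept with small-sample degrees of freedom in the between-arm models. Outcomes measured in the intervention group only, such as feasibility and acceptability, are not affected.
3. State in the analysis and discussion sections that, with one area per arm, the treatment effect cannot be separated from an area effect. Confidence intervals and p-values are then conditional on no area difference, and the conclusion must be limited accordingly.

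The second change repairs branch-level standard errors only; the third discloses the area confounding and does not remove it. The cost is a less favourable stated power, one model term and a more cautious conclusion. No extra participants are needed. Recruitment was to finish in December 2023, so a limit on enrolment per branch may no longer be possible; none of the three changes depends on one.

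### The 20% attrition allowance multiplies 188 by 1.2 instead of dividing by 0.8, so 226 recruits leave about 181 completers, not the 188 required

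*Protocol article*

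**What the plan says.** The Sample size section of the protocol article compares two means of systolic blood pressure. The design settings are given as "a power of 80%, a 1:1 ratio, and a 95% confidence interval were used", with the type I error described as "α = probability of type I error (usually 0.05"). The means and standard deviations come from an earlier Ethiopian trial in university staff. The result is "n1 = 94 and n2 = n1*1 = 94, Therefore, N = n1+n2 = 188".

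The allowance for loss follows directly: "By taking into account a 20% attrition rate, 226 total individuals or 113 individuals per group will be recruited for the study". No inflation formula is shown, and the 20% is not defined in any other way. The abstract repeats the total as "226 bank employees (age ≥18 years) with metabolic syndrome from government and private banks". The Randomization section makes the target operative, because screening continues until it is met.

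**The concern.** An attrition rate is the share of recruited participants who are later lost. To keep a required number of completers, that number is divided by one minus the rate. Multiplying by one plus the rate always gives too few, because the percentage is then taken of the completers instead of the recruits.

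If that is what was done here, the recruitment target, the attrition rate and the power cannot all be true together. The 94 per group is 93.9 rounded up, so the calculation has no spare margin to absorb the gap. At the attrition the plan itself expects, the comparison falls below the power for which it was sized.

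**Working it through.** **Inputs, all from the Sample size section:** standard deviations 15.0 and 16.3 mmHg (variances 225 + 265.69 = 490.69); means 107.8 and 114.2 mmHg (difference 6.4, squared 40.96); z-values 1.96 and 0.84 (sum 2.8, squared 7.84); 1:1 allocation; 20% attrition.

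**1. Reproduce the evaluable number.**
n per group = 490.69 × 7.84 / 40.96 = 93.92, rounded up to 94; total 188. The plan's figure is confirmed.

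**2. Reproduce the recruitment figure.** The step is not shown, so both usual forms were tried.

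| Form | Total | Per group |
|---|---|---|
| n × (1 + 0.20) | 188 × 1.2 = 225.6 → 226 | 94 × 1.2 = 112.8 → 113 |
| n / (1 − 0.20) | 188 / 0.8 = 235 | 94 / 0.8 = 117.5 → 118 (236 in total) |

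Only the first form yields the printed 226 and 113.

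**3. Completers from 226 at 20% attrition.**
226 × 0.8 = 180.8 in total; 113 × 0.8 = 90.4 per group. That is about 7 completers below 188. Expressed as recruits, the target is 9 short of 235, or 10 short of 236 (about 4%).

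**4. Attrition that 226 can absorb.**
226 − 188 = 38 losses; 38 / 226 = 16.8%. A 20% loss would be about 45 participants.

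**5. Power at 90.4 per group, same formula.**
Standard error = √(490.69 / 90.4) = 2.330. Then 6.4 / 2.330 − 1.96 = 0.787, which gives power of 78.4%. The t distribution gives 78.0%. At 94 per group the same calculations give 80.0% and 79.6%.

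**6. Check of the corrected target.**
236 × 0.8 = 188.8, or 94.4 per group; power 80.2% (normal approximation).

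**7. Can participants without follow-up still contribute?** The outcome sections schedule the metabolic measurements at baseline and month 9 only; month 6 is for feasibility and acceptability in the intervention group. A participant lost before month 9 therefore has no post-baseline systolic pressure, and the modified intention-to-treat rule of using all available data cannot restore the lost number.

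**The case against.** The strongest reply is that the error hardly matters. It costs about 1.6 percentage points of power, which is less than the uncertainty in a difference and standard deviations borrowed from one earlier study, or in the 20% itself. It biases nothing. This stands as a statement about size.

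A second reply is that the sample size formula ignores baseline values, whereas the abstract says the mixed models will account for them. If baseline systolic pressure enters as a covariate, residual variance falls by roughly 1 − r². The shortfall needs a factor of 90.4 / 94 = 0.962, so a correlation of about 0.20 between baseline and month 9 would recover 80%. A plain comparison of changes has relative variance 2(1 − r) and would need a correlation of about 0.52. The protocol gives no correlation, so both are assumptions. The point limits what can be said about the power finally achieved. It does not make the printed figures agree, because the Sample size section takes no credit for baseline adjustment.

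A third reply is that a corrected power figure could look more reliable than it is, since the formula assumes independent, individually randomised participants while the Randomization section assigns two city areas by coin toss. That is a fair caution about the wording of the correction, not a defence of 226.

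**Conclusion.** The concern holds. Under the protocol's own formula, recruiting 226, losing 20% and retaining 188 are incompatible. The plan would end with about 181 completers and about 78% power (78.4% by the normal approximation, 78.0% by t) instead of 80%. Holding 188 at 20% attrition takes 235 recruits, or 236 with equal arms.

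The multiplication by 1.2 is inferred, but the conclusion does not depend on it: 20% off 226 falls short of 188 however 226 was reached. The power figures assume the plan's means and standard deviations, equal loss in the two groups, no baseline adjustment and independent participants. The error is modest and does not threaten the validity of the trial. It should still be corrected, because a stated design figure is wrong.

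**What to change.** Correct the attrition sentence in the Sample size section in one of two ways:

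- Give 236 participants (118 per group) as the target that leaves 188 after 20% attrition, and change the total in the abstract to match. This means 10 more recruits.
- Keep 226 and state that it gives about 78% power at 20% attrition, or 80% power if attrition does not exceed 16.8%. This means no extra participants.

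The protocol expected recruitment to finish on 29 December 2023, so the second is probably the practical choice. Either way, show the inflation formula and say that the power assumes individual randomisation and independent observations. Neither option deals with the allocation by city area, which needs its own treatment. The cost is one sentence of text, plus the abstract figure if the target changes.
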